## 1. STUDY OBJECTIVE

### 1.1. Primary objective

The primary outcomes of the study were the seroconversion rates and seropositive rates of anti-pertussis antibodies in the co-purified DTaP group, as well as a comparison of seroconversion rates and seropositive rates of anti-diphtheria and anti-tetanus antibodies in the co-purified DTaP and DT groups.

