## Supplementary information

| Contents                                                                                                                                                                                | Page |
|------------------------------------------------------------------------------------------------------------------------------------------------------------------------------------------------|-------------|
| Supplementary Table 1. Seroconversion rates to co-purified DTaP or DT before and day 28 after vaccination based on subgroups that were positive or negative for antibodies at baseline. | 2           |
| Protocol                                                                                                                                                                                | 3-18        |
| CONSORT 2010 checklist                                                                                                                                                                  | 19-20       |

**Supplementary Table 1.** Seroconversion rates to co-purified DTaP or DT before and day 28 after vaccination based on subgroups that were positive or negative for antibodies at baseline.

| Baseline antibody | co-purified DTaP |              | DT  |              | P |
|-------------------|------------------|--------------|-----|--------------|----------|
|                   | N                | Rate, n (%)  | N   | Rate, n (%)  |          |
| anti-PT    |                  |              |     |              |          |
| ≥20 IU/ml         | 21               | 11(52.38)    | 8   | 0(0)         |          |
| < 20 IU/ml        | 213              | 179 (84.04)  | 216 | 5 (2.31)     |          |
| anti-FHA   |                  |              |     |              |          |
| ≥20 IU/ml         | 85               | 31 (36.47)   | 69  | 0(0)         |          |
| < 20 IU/ml        | 149              | 143 (95.97)  | 155 | 8 (5.16)     |          |
| anti-DT    |                  |              |     |              |          |
| ≥0.1 IU/ml        | 87               | 87 (100.00)  | 77  | 77 (100.00)  | 1.000    |
| < 0.1 IU/ml       | 147              | 147 (100.00) | 147 | 147 (100.00) | 1.000    |
| anti-TT    |                  |              |     |              |          |
| ≥0.1 IU/ml        | 214              | 207 (96.73)  | 203 | 174 (85.71)  | <0.001   |

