|                   | 
enrollment is 240. Blood samples will be collected before immunization on D0 and the subjects will then be vaccinated with the co-purified DTaP (0.5 mL/vaccine); blood samples will be collected on D28.
 
Control group is the DT group: The target number of enrollment is 240. Blood samples will be collected before immunization on D0 and the subjects will then be vaccinated with the DT (0.5 mL/vaccine); blood samples will be collected on D28.
                                                                                                                                                        |
| Hypotheses | 
1.The seroconversion rate of pertussis antibody in 6-year-old children vaccinated with co-purified DTaP vaccine is not less than 70%.
 
2. There was no significant difference in the seroconversion rates of diphtheria and tetanus antibodies between 6-year-old children vaccinated with co-purified DTaP vaccine and DT.
                                                                                                                                                                                                                                                                                       |
| Vaccines   | 
Vaccine 1: co-purified DTaP
 
Manufacturer: Chengdu Institute of Biological Products Co., Ltd.
 
Strength: 0.5 mL/vial/dose, the titer of acellular pertussis vaccine, diphtheria vaccine and tetanus vaccine shall not be lower than 4.0 IU, 30 IU and 40 IU respectively.
 
Vaccine lot no.: 20220311
 
Vaccine 2: DT
 
Manufacturer: Wuhan Institute of Biological Products Co., Ltd.
 
Strength: 0.5 mL/vial/dose, the titer of diphtheria toxoid is not less than 30IU; the titer of tetanus toxoid should not be lower than 40IU.
 
Vaccine lot no.: 202112020-2
 |

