## **1.2 Secondary objective**

The secondary outcomes of the study were the seroconversion rates and seropositive rates of anti-pertussis antibodies in the co-purified DTaP group, as well as a comparison of seroconversion rates and seropositive rates of anti-diphtheria and anti-tetanus antibodies in the co-purified DTaP and DT groups.

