### **3.3 Immunogenicity Assessment**

Concentrations of antibodies against pertussis, diphtheria, and tetanus were measured by the Enzyme-Linked Immunosorbent Assay (ELISA) method.

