#### **Immunogenicity assessment criteria for diphtheria vaccine or tetanus vaccine:**

Positive: Antibody titer is  $\geq 20$  IU/mL.

Seroconversion: Antibody concentration is  $< 20$  IU/mL before immunization and  $\geq 20$  IU/mL after immunization; or antibody concentration is  $\geq 20$  IU/mL before immunization and is increased  $\geq 4$ -fold after immunization.

Antibody level: Geometric mean concentrations (GMCs) of serum antibody before and after pertussis vaccine immunization as well geometric mean increase (GMI) in serum antibody

after immunization.

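### The diphtheria comparison of DTaP with DT rests only on dichotomised rates, which were 100% for seroconversion in both arms and say little about antibody level; the D28 GMC ratio should be added beside them

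*Combined protocol and SAP*

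**What the plan says.** Section 1.1 gives the primary between-arm outcome as "a comparison of seroconversion rates and seropositive rates of anti-diphtheria and anti-tetanus antibodies in the co-purified DTaP and DT groups". Hypothesis 2 in the Protocol Synopsis is narrower: "There was no significant difference in the seroconversion rates of diphtheria and tetanus antibodies". Section 1.2 repeats the outcomes of 1.1, beginning "The secondary outcomes of the study were the seroconversion rates and seropositive rates of anti-pertussis antibodies in the co-purified DTaP group", so no concentration outcome appears at the secondary level either.

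The underlying measurement is continuous. Section 3.3 states: "Concentrations of antibodies against pertussis, diphtheria, and tetanus were measured by the Enzyme-Linked Immunosorbent Assay (ELISA) method". Section 3.2 has serum drawn from every child before vaccination and on D28. Under the diphtheria and tetanus criteria, 3.3 lists "Geometric mean concentrations (GMCs) of serum antibody before and after pertussis vaccine immunization as well geometric mean increase (GMI) in serum antibody". No objective, hypothesis or between-arm test in the available text is attached to these quantities.

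Supplementary Table 1 reports diphtheria seroconversion by baseline status at 0.1 IU/ml. The entries from the DTaP count onward are "87 (100.00) | 77 | 77 (100.00) | 1.000" for children at or above the cut and "147 (100.00) | 147 | 147 (100.00) | 1.000" for those below it. Its footnote names a two-sided chi-square or Fisher's exact test.

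**The concern.** A DT control arm allows a check on whether a pertussis-containing booster weakens the diphtheria and tetanus responses. A responder rate shows such a loss only if it pushes enough children below the criterion. Where every child in both arms responds, the rate has no variation left, and P = 1.000 would be returned for any GMC ratio that leaves every child a responder.

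About two thirds of the children were below 0.1 IU/ml at baseline (147/234 = 63% and 147/224 = 66%). Under the table's cut they count as seroconverters at any D28 value at or above it. A reader could take the result as evidence of an equal diphtheria antibody response, which it is not, although the trial holds the concentrations that could address that question.

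**Working it through.** **The plan's own figure.** Section 3.7 gives no power for the diphtheria comparison. Its 240 per group comes from the 70% pertussis target (two-sided 0.05, 90% power, 15% loss) and the expected rate is not stated. Assuming 80%: n = [1.96 × √(0.7 × 0.3) + 1.2816 × √(0.8 × 0.2)]² / 0.10² = 1.411² / 0.01, about 200, and 200/0.85 = 236, close to 240. That says nothing about diphtheria.

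**Inputs.**
- Evaluable per arm: 240 × 0.85 = 204 (3.7).
- Two-sided alpha: 0.05.
- Observed diphtheria seroconversion: DTaP 87/87 + 147/147 = 234/234; DT 77/77 + 147/147 = 224/224 (Supplementary Table 1).
- Assumed, not in the documents: log10-normal concentrations with SD 0.4, 0.5 or 0.6.
- Assumed true DT failure rate p0: 0.1%, 0.5% or 1.33%. The last is the one-sided 95% upper bound from 0/224: 1 − 0.05^(1/224) = 1.33%.

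**Step 1: what the rates establish.** The Newcombe 95% CI for 234/234 minus 224/224 runs from about -1.6 to +1.7 percentage points.

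**Step 2: failures needed for significance.** Against 0/204, Fisher's test gives p = 0.061 with five failures in the other arm and p = 0.030 with six. At least six are needed.

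**Step 3: power on log concentration.** Let d = −log10(GMC ratio) and SE = SD × √(2/204). For ratio 0.67 and SD 0.5, d = 0.174 and SE = 0.0495, so d/SE = 3.51 and power is 94% (two-sample t, noncentral t distribution).

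**Step 4: power on seroconversion.** The same shift implies a DTaP failure rate of Φ(Φ⁻¹(p0) + d/SD). For p0 = 0.1%, ratio 0.67 and SD 0.5 this is Φ(−3.090 + 0.348) = 0.31%, or 0.6 expected failures in 204 when six are needed. Fisher power was obtained by exact enumeration.

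| GMC ratio (DTaP/DT) | SD (log10) | Power, log concentration | Fisher, p0 = 0.1% | Fisher, p0 = 0.5% | Fisher, p0 = 1.33% |
|---|---|---|---|---|---|
| 0.67 | 0.4 | 99% | 0% | 5% | 22% |
| 0.67 | 0.5 | 94% | 0% | 2% | 12% |
| 0.67 | 0.6 | 83% | 0% | 1% | 8% |
| 0.5 | 0.4 | >99.9% | 1% | 43% | 81% |
| 0.5 | 0.5 | >99.9% | 0% | 19% | 52% |
| 0.5 | 0.6 | 99.9% | 0% | 9% | 33% |

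**Step 5: could a real loss sit behind 234/234?** With SD 0.5 and p0 = 0.1%, a halved GMC implies 0.64% failures on DTaP, and the chance of seeing none in 234 is (1 − 0.0064)^234 = 22%. With p0 = 0.01% it is 81%. For a one-third loss the two figures are 49% and 92%.

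**Step 6: precision of the proposed estimate.** The 95% CI of the GMC ratio would extend by a factor of 10^(1.96 × SD × √(2/204)) = 1.20, 1.25 or 1.31 either side of the estimate at SD 0.4, 0.5 or 0.6.

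**Contrast with tetanus.** DTaP 207/214 + 20/20 = 227/234 (97.0%); DT 174/203 + 21/21 = 195/224 (87.1%). Tetanus seroconversion is not at ceiling and separates the arms.

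**Sensitivity.** At SD 0.8, power on log concentration falls to about 60% for a one-third loss and 97% for a one-half loss. At SD 0.3, with 234 against 224 children and p0 of about 1.3%, Fisher power rises to 58% and above 99%. The model treats seroconversion as crossing one cut. For children at or above 0.1 IU/ml at baseline (87/234 and 77/224) it requires a fourfold rise, so the model is approximate there.

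**The case against.** The strongest reply is that the plan asks whether the proportions responding differ, and the data answer that within about 1.7 points. A reader might infer that the trial cannot answer its primary diphtheria question; the documents do not support that. The rate question is answered. What goes unanswered is a different question, about antibody level, and nothing in the documents says how large a GMC loss would matter when every child responds. Preferring rates is a legitimate choice of estimand.

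A reader might also infer that the rates have almost no power even against a halving. That holds only if true DT failure is very low: at 0.5% to 1.33%, Fisher power for a halving is 9% to 81%.

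Three further points stand. The 100% is a trial result, not a planning assumption, so promoting GMC now carries hindsight. The ceiling is shown only at the table's 0.1 IU/ml cut; section 3.3 prints 20 IU/mL for diphtheria and tetanus and 0.1 IU/mL for pertussis, the reverse of the table, and these must be reconciled. Finally, 3.3 already lists GMC and GMI (the geometric mean increase), the available text has no statistical methods section, and some of the document is not available, so a planned GMC comparison elsewhere cannot be excluded. It would still not be part of 1.1 or Hypothesis 2 as they stand.

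None of this removes the case for stating the GMC comparison beside the rates.

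**Conclusion.** The concern holds in a limited form. The diphtheria comparison in 1.1 and Hypothesis 2 uses rates only, and diphtheria seroconversion as reported is at ceiling, so it gives close agreement on responder rates and little information on antibody level. For a one-third GMC loss, log concentration has at least 75 percentage points more power than Fisher's test in every cell of the table (the smallest gap is 83% against 8%). For a one-half loss the advantage runs from about 19 points (SD 0.4, p0 = 1.33%) to nearly 100. These sizes depend on the assumed SD and DT failure rate, neither of which the documents give.

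A reader might conclude that the rates should be demoted to secondary outcomes. The documents do not support that: the rates answer the question the plan set, and the tetanus rate discriminates between the arms.

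**What to change.** In 1.1 and Hypothesis 2, add the D28 anti-diphtheria GMC ratio (DTaP/DT) with its 95% CI, analysed on log concentration, as a comparison alongside the seroconversion and seropositive rates. Keep the diphtheria and tetanus rates where they are. A tetanus GMC ratio may be added but should not replace the rate. State that P = 1.000 on diphtheria seroconversion is not evidence of equal antibody response. Because results are already known, label the GMC comparison as added after the original plan. Reconcile the cut-offs in 3.3 with those in Supplementary Table 1.

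The cost is wording and one more stated comparison, on a scale less directly read as protection than a rate. The concentrations are already measured, so no further children, samples or assays are needed.

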## **1.2 Secondary objective**

The secondary outcomes of the study were the seroconversion rates and seropositive rates of anti-pertussis antibodies in the co-purified DTaP group, as well as a comparison of seroconversion rates and seropositive rates of anti-diphtheria and anti-tetanus antibodies in the co-purified DTaP and DT groups.

## **3. TRIAL DESIGN**

### **3.1 Design**

This trial uses a randomized, controlled, open-label design to evaluate the safety and immunogenicity of the booster dose of co-purified DTaP or DT at children aged 6 years.

This study plans to enroll 480 subjects who will be randomized into 2 groups with 240 subjects per group.

#### **Randomization:**

The participants were randomly assigned (1:1) to one of two group schedules using a random number table by block randomization. There are a total of 60 blocks with a block length of 8. All eligible subjects were assigned a random number which was used to identify all procedures performed after the subjects had been randomly grouped. Once a random number had been assigned to one subject, it could not be reassigned to another subject.

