### 3.4 Safety Data Collection

Subjects are observed for 30 min after immunization. Diary cards are distributed after immunization and the subjects must record all solicited and unsolicited adverse events (AEs) observed from D0 to D28 post-immunization in the diary cards every day. Adverse events following immunization (AEFI) will be collected by the investigator using the AEFI monitoring system at 6 months after full immunization. Serious adverse events (SAEs) will also be passively collected at 6 months after full immunization.

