## 4.2 Exclusion Criteria

### Exclusion criteria for first dose

- ✕ allergy to any ingredient of the vaccine;
- ✕ past history of serious allergies to any immunization;
- ✕ medical or family history of convulsion, epilepsy, cerebral diseases and mental diseases;
- ✕ patient with immunodeficiency, has received immunosuppressants (oral steroids) during the treatment of malignant tumors or has HIV-induced immune impairment, or presence of congenital immune disease in close family member;
- ✕ injection of non-specific immunoglobulin within 1 month before enrollment;
- ✕ has acute febrile and infectious diseases;
- ✕ definite diagnosis of thrombocytopenia or history of other coagulopathy that may cause subcutaneous injection to be contraindicated;
- ✕ patient with serious chronic disease or in the acute phase of a chronic disease, or with uncontrolled hypertension or diabetes;
- ✕ various infectious, purulent, and allergic skin diseases;
- ✕ any other conditions that the investigator determines may impact the trial assessments.

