| Randomisation:            |         |                                                                                                                                                                                             |                     |
| Sequence generation              | 8a      | Method used to generate the random allocation sequence                                                                                                                                      | 13                  |
|                                  | 8b      | Type of randomisation; details of any restriction (such as blocking and block size)                                                                                                         | 13                  |
| Allocation concealment mechanism | 9       | Mechanism used to implement the random allocation sequence (such as sequentially numbered containers), describing any steps taken to conceal the sequence until interventions were assigned | 13                  |
| Implementation                   | 10      | Who generated the random allocation sequence, who enrolled participants, and who assigned participants to interventions                                                                     | 13                  |
| Blinding                         | 11a     | If done, who was blinded after assignment to interventions (for example, participants, care providers, those                                                                                | NA                  |

|                                                      |     |                                                                                                                                                   |             |
|------------------------------------------------------|-----|---------------------------------------------------------------------------------------------------------------------------------------------------|-------------|
|                                                      |     | assessing outcomes) and how                                                                                                                       |             |
| Statistical methods                                  | 11b | If relevant, description of the similarity of interventions                                                                                       | NA          |

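### One fixed block length of 8, printed in an open-label protocol, would let staff who see the whole sequence deduce on average 20% of assignments; varied, withheld block lengths and late release would remove most of that certainty

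*Combined protocol and SAP*

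**What the plan says.** Protocol section 3.1, under Randomization, sets out the method: "The participants were randomly assigned (1:1) to one of two group schedules using a random number table by block randomization". It then fixes the block structure: "There are a total of 60 blocks with a block length of 8". The only handling rule is "Once a random number had been assigned to one subject, it could not be reassigned to another subject". Numbers go to eligible subjects, so eligibility is meant to come before assignment.

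Section 3.1, under Design, describes the blinding and the size: "This trial uses a randomized, controlled, open-label design" and "This study plans to enroll 480 subjects who will be randomized into 2 groups with 240 subjects per group".

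The last exclusion criterion in section 4.2 is a matter of judgement: "any other conditions that the investigator determines may impact the trial assessments".

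The protocol text does not say who holds the list, whether those who enrol are separate from those who assign, how the next assignment is hidden, or whether one list serves one site or several. The CONSORT checklist item on concealment, which asks for a description of the mechanism, "describing any steps taken to conceal the sequence until interventions were assigned", points to page 13 of the report. That page is not among the documents.

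**The concern.** With 1:1 allocation, a block of 8 holds four children per arm. Once four have gone to one arm, the rest of the block is known. Hiding the list does not prevent this: the deduction needs only the block length, the block's starting point and the assignments already made. The protocol prints the first, and open-label delivery can reveal the last.

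Foreknowledge does harm only if it changes who enters. The discretionary exclusion criterion is one route by which it could. The comparisons at risk are those between the arms: diphtheria and tetanus responses, which are among the primary outcomes in section 1.1 and the subject of Hypothesis 2 in the synopsis, and safety. A bias in who enters acts before any serum is read, so an objective ELISA result does not protect against it, and analysis cannot fully undo it.

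**Working it through.** **Inputs.** Section 3.1: 1:1 allocation, 60 blocks of length 8, 480 children, open-label. Assumed, because the protocol is silent: the observer sees every earlier assignment in order on one list and knows where each block starts.

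**The plan's own figure.** 60 × 8 = 480, and 60 × 4 = 240 per arm. Both match section 3.1.

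**Certain assignments.** A 4:4 block has C(8,4) = 70 equally likely orderings. A place is certain if one arm has already filled its four places:

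- Places 1 to 4: never.
- Place 5: 2 × C(4,4) = 2 of 70 orderings (2.9%).
- Place 6: 2 × C(5,4) = 10 of 70 (14.3%).
- Place 7: 2 × C(6,4) = 30 of 70 (42.9%).
- Place 8: 70 of 70 (100%).

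The sum is (2 + 10 + 30 + 70)/70 = 112/70 = 1.6 per block. The closed form for length 2m agrees: 2m/(m + 1) = 8/5 = 1.6. The share is 1.6/8 = 20%, and the expected total is 60 × 1.6 = 96 (SD about 6). The floor is one per block: 60 of 480, or 12.5%.

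**Best guess.** The observer always guesses the arm that is behind and tosses a coin when the arms are level. Expected correct guesses per block are m + (2^(2m)/C(2m,m) − 1)/2 = 4 + (256/70 − 1)/2 = 4 + 1.33 = 5.33. The rate is 5.33/8 = 66.6%, against 50% by chance.

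**If sites share blocks.** Assume that children from several sites fall at random into common blocks, that each site sees only its own children, and that block boundaries are known. Simulation gives about 1.3% certain with two sites, 0.25% with three and 0.07% with four.

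**Alternatives.** The observer again sees the full sequence. For mixed blocks the observer knows the set of lengths but not their order; for the maximum-imbalance list the observer knows the cap. Rows 2 to 4 were simulated on lists of 480.

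| Scheme | Certain | Best guess correct |
|---|---|---|
| Fixed 8 (plan) | 20% | 66.6% |
| Random 4, 6, 8 | about 2% | 68% |
| Random 8, 12, 16 | about 1.6% | 64% |
| Maximum imbalance 4 (big stick) | about 12% | 56% |

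The last row can be checked by hand. In the long run such a list sits at its cap 1/(2 × 4) = 12.5% of the time, and every assignment there is forced. The guess rate is then 12.5% + 87.5%/2 = 56.25%.

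Mixing in smaller blocks removes certainty but makes guessing slightly easier. Mixing larger blocks removes nearly all certainty and lowers guessing by about 2.5 points. The capped list does best on guessing but leaves about 59 of 480 assignments certain.

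**The case against.** The strongest reply is that the 20% is conditional and that the documents do not establish the conditions. They do not show that enrolling staff saw one running sequence, knew where blocks began, or had the protocol's block length during recruitment. Concealment and roles may be described on the report page that the CONSORT checklist cites. This stands, and it is why the figure is stated with its conditions.

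Second, the consequences are limited. The pertussis hypothesis, which drives the sample size in section 3.7, compares one arm with 70% and does not depend on the allocation. Supplementary Table 1 shows 100% diphtheria seroconversion in both arms at both baseline levels, which leaves that result no visible room to be shifted. Section 3.2 has D0 serum stored frozen, and no D0 result is said to be available at enrolment, so staff would need some other cue to select on. All of this stands. It limits the likely harm without making the sequence less deducible, and tetanus and safety remain exposed in principle.

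Third, subjective diary reporting comes from open-label delivery, and no block scheme changes it. That is right. The safety exposure meant here is selective entry alone.

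A reader might go further and infer that staff did steer entry, and might cite baseline anti-PT at or above 20 IU/ml in Supplementary Table 1: 21 of 234 against 8 of 224 (Fisher p = 0.021). The documents do not support this. The other three antigens are balanced (p = 0.24, 0.56 and 0.87), one difference in four at this level is compatible with chance, and antibody status is not stated to be known at entry.

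**Conclusion.** The point holds as a conditional design weakness with a cheap remedy. For staff who see all earlier assignments on one list and know the block length and block starts, on average 96 of 480 assignments (20%) are certain, never fewer than 60, and the best guess is right 66.6% of the time. If blocks are shared across sites that see only their own children, certainty could be near 1% or below.

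It would be wrong to read this as saying that 20% of assignments were known in advance, or that entry was steered. The first needs facts about list access that the protocol does not give, and nothing in the documents shows the second. The protocol's silence on concealment does not show that concealment was absent. The exposure is confined to selection bias in the diphtheria, tetanus and safety comparisons between the arms.

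**What to change.** In section 3.1, under Randomization:

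1. Replace the single length with larger lengths varied at random, for example 8, 12 and 16.
2. Move the lengths to a document withheld from enrolling staff, and state in the protocol only that blocks of varying size are used.
3. State who holds the list, and release each assignment only after eligibility and the D0 blood draw have been recorded. Section 3.1 already places that draw before vaccination, so the visit schedule need not change.

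The first step alone cuts certain assignments from 20% to about 1.6% but leaves guessing at about 64%, so the second and third are needed with it. A maximum-imbalance list with a cap of 4 is an alternative if lower guessing is preferred (56%). It leaves about 12% of assignments certain to anyone who knows the cap, so the cap would also have to be withheld.

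The cost is a regenerated list and one edited paragraph. The final split may miss 240/240 by a few children. If enrolment stops at 480 halfway through a block of 16, the difference between arms is at most 8, that is 244/236; with a cap of 4 it is at most 242/238.
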